### **4.3 Handling of missing or incoherent data**

We assess the distribution of all variables and the extent of missingness. Outlier or incoherent data will be discussed and addressed by consensus among the investigative team. Given the nature of health care utilization recorded in the clinical data warehouse and claims database, it is not expected that the primary and secondary outcomes data would be missing.

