### **12.2 Sample Size Determination**

*Sample Size.* We derived the sample size that is needed to detect an overall difference which is of clinical significance and with potential cost-saving implications. We have powered our study to detect the primary outcome (10% relative reduction in overall hospital admissions and overall ED visits) at 12 months. We estimate 1,500 BACO members are eligible intermediate risk patients. We know from existing institutional data that these intermediate risk BACO members experience an average of 4.3 inpatient admission over 12 months, and 10.2 ED visits over 12 months. With these baseline data, we estimate that a total sample size of 364 patients (N=182 in each arm) is adequate to detect a 10% reduction in total ED plus hospital visits with statistical power of 0.90 and two-sided type I error rate of 0.05, accounting for 80% retention over a 12-month study period.

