| Duration of follow-up | 12 months                                                                                                                                                                                                                                                                                                                                                                                                                                                                                                                                                                                                                                                                                                                                                                                                                                                                                                                                                                                                                                                                                                     |
| Criteria for efficacy | 
Measures:
We collect data on demographics (age, gender, race, ethnicity, and language), insurance coverage (proportion of days covered from claims data), and on potential confounding variables, such as medical comorbidity as measured by a validated comorbidity index (the Charlson Comorbidity Score), mental health and substance use diagnoses, health-related social needs screening results, and medication adherence using a measure of proportion of days covered based on pharmacy claims data.
 
Primary end points:
Our primary outcome is the percentage change in all-cause hospital admissions and all-cause emergency department visits (a composite outcome) in the 12 months following enrollment.
 
Secondary end points:
Secondary outcomes include all-cause hospital admissions and all-cause emergency department visits as separate outcomes, all-cause 30-day hospital readmissions, 30-day ED revisit rates, and connection to resources (referral to food pantry, visits to food pantry, utility shutoff protection letters).
 |

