## **5.4 Calculation of the outcome**

A composite measure is created by summing all-cause hospital admissions and all-cause emergency department visits (a composite outcome) in the 12 months following enrollment.

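### The primary visit count has no exposure offset and no rule for death or disenrolment, so time that cannot be observed is implicitly treated as event-free

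*Combined protocol and SAP*

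**What the plan says.** - **Outcome.** SAP 5.4 builds the composite by "summing all-cause hospital admissions and all-cause emergency department visits" over the 12 months after enrolment. The sum is not divided by time observed.
- **Models.** The Statistical method row of the SAP's opening table and SAP 5.1 describe a zero-inflated negative binomial model. The opening table adds count-model alternatives and a logistic sensitivity analysis of any utilization, and promises rate ratios. Neither place mentions an offset, person-time, censoring, death or disenrolment.
- **Missing data.** SAP 4.3 undertakes to assess the extent of missingness. It then says that, given the warehouse and claims sources, "it is not expected that the primary and secondary outcomes data would be missing". It gives no method in case they are.
- **Retention.** Protocol 12.2 sizes the trial "accounting for 80% retention over a 12-month study period". SAP 3.3 repeats the same number and power with no mention of loss.
- **Membership.** Protocol 7.1 requires the risk tier within ACO membership only at enrolment; nothing requires it to continue.
- **Coverage.** Protocol 12.3 and the Measures text of the SAP's opening table list "insurance coverage (proportion of days covered from claims data") among the variables collected. Neither ties it to the outcome model.
- **Sources.** Protocol Table 1 lists both plan claims and the hospital's clinical data warehouse for every utilization outcome. Protocol 11.2 assigns the utilization outcomes to claims in one item and takes study outcomes from the warehouse in another. No section says how the two are combined.

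**The concern.** A count over a fixed year is comparable between patients only if each could be observed for that year. A patient who dies stops generating visits in either source. A patient who leaves the plan stops generating claims, so visits to other hospitals have no listed source. With no offset or censoring rule, the model reads these gaps as low utilization, which is the direction the trial hopes to find. The reported zeros are out of all 364 patients and the primary analysis is intent-to-treat, so everyone appears to receive a count however long they were observable.

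At stake are the rate ratio, if observed time differs between arms, and the mean visits per arm that SAP 5.3.2 will report, even if it does not. The zero-inflation part and the any-visit model are exposed too, because a short observation period makes a zero more likely.

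**Working it through.** **1. Reproduce the planned sample size.** Inputs from protocol 12.2: members "experience an average of 4.3 inpatient admission over 12 months, and 10.2 ED visits over 12 months", so the control mean is 4.3 + 10.2 = 14.5. The effect is a "10% relative reduction in overall hospital admissions and overall ED visits", so the difference is 1.45. The design has "statistical power of 0.90 and two-sided type I error rate of 0.05". The SD is not stated; a Poisson SD of √14.5 = 3.81 is assumed.

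n per arm = 2 × (1.96 + 1.2816)² × 14.5 / 1.45² = 144.9, so 145. Then 145 / 0.8 = 181.25, so 182 per arm and 364 in total.

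This matches the plan exactly, and under this formula only with the 20% allowance. With no loss, 145 per arm would do, and 182 per arm would have 95.3% power. SAP 3.3 still states 90%.

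**2. Equal loss.** Let L be the share lost, f the fraction of the year observed in those lost, and c the share of later visits still captured. L, f and c are assumptions; the documents report no loss by arm. The expected count is multiplied by g = 1 − L(1 − f)(1 − c).

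With L = 20% in both arms and c = 0:

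| f | Observed mean (true 14.5) | Under-count |
|---|---|---|
| 0.25 | 12.3 | 15% |
| 0.50 | 13.05 | 10% |
| 0.75 | 13.8 | 5% |

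The factor g cancels in the ratio, so the rate ratio is unchanged.

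**3. Unequal loss, no true effect.** The spurious ratio is g(THRIVE+) / g(control). For f = 0.5 (loss uniform over the year) and c = 0, with 25% lost on THRIVE+ and 15% on control: (1 − 0.125) / (1 − 0.075) = 0.875 / 0.925 = 0.946. Reversed: 1.057.

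| f | c = 0: 25/15 | c = 0: 15/25 | c = 0.5: 25/15 | c = 0.5: 15/25 |
|---|---|---|---|---|
| 0.25 | 0.915 | 1.092 | 0.960 | 1.041 |
| 0.50 | 0.946 | 1.057 | 0.974 | 1.027 |
| 0.75 | 0.974 | 1.027 | 0.987 | 1.013 |

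A true ratio of 0.90 would appear as 0.9 × 0.946 = 0.851, or 0.9 × 1.057 = 0.951 if reversed (f = 0.5, c = 0).

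**4. Cost of an offset.** With 20% lost per arm, person-years per arm are 182 × (0.8 + 0.2f) = 154.7, 163.8 and 172.9 for f = 0.25, 0.5 and 0.75. Power for a ratio of 0.90 under the same Poisson variance is 92%, 93% and 94% by the means formula, and 93%, 94% and 95% on the log rate ratio. These powers are optimistic. The SAP reports 136 zeros in 364 (37%), whereas a Poisson count with mean 14.5 gives a zero with probability e^(−14.5), about 5 × 10⁻⁷. They show only that the offset does not break the plan's own power calculation.

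**The case against.** The strongest reply is that outcomes are collected passively from two sources, so little is lost. Participants are primary care patients of the hospital, and no section restricts warehouse records to current plan members. Losing coverage therefore need not erase on-site visits. This stands, and it shrinks the figures (the c = 0.5 columns). It does not cover visits elsewhere after disenrolment, or time after death.

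A second reply is that coverage days are collected and could be adjusted for. Under SAP 5.1 they would enter only if found to differ significantly between arms. A post-enrolment covariate chosen by a significance test is not an exposure offset.

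Third, with a common 12-month window a rate ratio is meaningful without an offset. That is true if follow-up is complete, which is the assumption in question.

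The documents do not support several stronger readings that a reader might infer:

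- *Patients who are lost are scored as zero.* No section says so. Visits before loss are in the sum; a patient scores zero only if none was recorded.
- *The 20% allowance contradicts SAP 4.3.* Protocol 12.2 does not define retention. It may mean staying in a voluntary program of monthly contacts, which is compatible with complete outcome data.
- *The error favours THRIVE+.* If navigation kept patients covered longer, it would work against THRIVE+. Insurance is not among the listed THRIVE domains, so any effect on coverage is conjecture.
- *The 37% zeros are uncovered time.* Some may be, but the SAP gives no cause.

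**Conclusion.** The gap is real: a raw 12-month sum, no offset in any model, no rule for death or disenrolment, and a stated expectation that nothing will be missing. The plan as written treats time after death, and visits to other hospitals after disenrolment, as event-free.

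Whether this biases the trial's result cannot be told from the documents. With equal loss of similar timing in both arms, the rate ratio is roughly unbiased and only the mean counts are too low. With the assumed 25% vs 15% loss, spread uniformly, the ratio moves by about 5 to 6% with no later capture and about 3% with half capture, in either direction, against a 10% target effect. The trial's own loss may be smaller; without coverage and deaths by arm, a reader could not judge. The change is worth making because it replaces a stated analysis with a better one at little cost, not because a bias has been shown.

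Protocol 12.2, SAP 3.3 and SAP 4.3 must be reconciled, since 364 carries a 20% allowance that the SAP neither repeats nor explains.

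**What to change.** 1. Define observed days as days alive and enrolled in the plan within 365 days of enrolment, and count events over that same window.
2. Use log(observed days) as the offset in the primary and secondary count models, and include it in the zero-inflation part and the any-visit logistic model.
3. State how claims and warehouse records are combined. Add a sensitivity analysis that keeps warehouse visits after disenrolment.
4. Report covered days, disenrolments and deaths by arm. Treat any analysis of patients covered for the full year as supportive only, because it conditions on something that happens after assignment.
5. Replace the sentence in SAP 4.3 on missing outcomes. Say in protocol 12.2 whether 80% retention refers to program engagement or to outcome data, and carry that into SAP 3.3.
6. Since the SAP already cites the observed number of zero counts, label the change as made after data were seen and show the analysis without the offset beside it.

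The cost is SAP wording and a small amount of extra analysis. Coverage days are already to be collected; death dates are not listed among the variables and may need to be extracted. One limit remains: the offset takes the visit rate while observed to stand for the unobserved time, which is why items 3 and 4 belong with it.

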### **4.4 Statistical software**

We use SAS Version 9.4 to conduct all statistical analyses (SAS Institute Cary, NC).

## **5. Primary outcome analysis**

### **5.1 Definitions**

Our primary outcome is all-cause hospital admissions and all-cause emergency department visits (a composite outcome) in the 12 months following enrollment. We compare baseline characteristics of participants using two-sample t tests for continuous variables or Chi-square tests for categorical variables. We assess the distribution of the outcome variables, diagnose error terms in residual analysis, and use appropriate link functions (e.g., normal link function for continuous outcomes with normal distribution) to construct linear regression models to assess the treatment effect. We will further assess any potential collinearity among covariates by evaluating variance inflation factors and correlation matrices. In the case where there are excess zeros (e.g., no visits), we employ a zero-inflated negative binomial model, which is a two-part model that examines simultaneously the odds of any visit, and the rates of visits among those patients who had any health care utilization. In the adjusted regression models, we will control for any factors including baseline utilization that are found statistically significant between the two arms.

## **5.2 Amended definitions**

None

## **5.3 Trial monitoring**

### **5.3.1 Interim analyses**

We will conduct a 6-month interim analysis to assess data quality, examine distribution of variables and potential incoherence, and conduct preliminary analyses to detect between-group difference in health care utilization at 6-month follow up.

### **5.3.2 Presentation of results**

We examine descriptive statistics of all variables. For categorical variables, we will report proportions, and for continuous variables, we will report means, standard deviations, and ranges. We will assess the randomness of treatment assignment according to odd versus even patient medical record number by comparing patient characteristics by treatment status. In order to determine if the enhanced usual care intervention achieves a greater reduction (or smaller increase) in all-cause hospital admissions and all-cause emergency department visits (our composite primary outcome), respectively, in the 12 months following enrollment compared to the usual care condition, we report and compare groups on their average number of visits in the 12 months post-enrollment controlling for potential baseline differences and any covariates (e.g., age, gender) determined *a priori* as important predictors of healthcare utilization. We will note differences that are statistically significant at the  $\alpha < 0.05$  level. In the adjusted regression models, we control for any factors including baseline utilization that are found statistically significant between the two arms.

## **5.4 Calculation of the outcome**

A composite measure is created by summing all-cause hospital admissions and all-cause emergency department visits (a composite outcome) in the 12 months following enrollment.

## **5.5 Subgroup analyses**

In order to assess whether the presence of comorbid mental health and substance use diagnoses, race, and language may modify the treatment effect, we evaluate interaction terms between these pre-determined potential moderators and the treatment variable in the overall sample, and further conduct stratified analyses among these potential modifiers to assess the robustness of any differential effects if detected above. We conduct stratified analyses where we have adequate sample size (age, gender, race, language).

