We will first examine descriptive statistics of all variables. For categorical variables, we will report proportions, and for continuous variables, we will report means, standard deviations, and ranges. We will assess the randomness of treatment assignment according to odd versus even patient medical record number by comparing patient characteristics by treatment status. In order to determine if the THRIVE+ condition achieves a greater reduction (or smaller increase) in all-cause hospital admissions and all-cause emergency department visits (our composite primary outcome) in the 12 months following enrollment compared to the THRIVE-Basic condition, we will compare groups on their average number of visits in the 12 months post-intervention period controlling for potential baseline differences and any covariates (e.g., age, gender) determined *a priori* as important predictors of healthcare utilization. We will note differences that are statistically significant at the  $\alpha < 0.05$  level. We will assess the distribution of the outcome variables, diagnose error terms in residual analysis, and use appropriate link functions (e.g., normal link function for continuous outcomes with normal distribution) to construct linear regression models to assess the treatment effect. We will further assess any potential collinearity among covariates by evaluating variance inflation factors and correlation matrices. The primary analyses will be based on intent-to-treat. Because participants may receive varying “doses” of the THRIVE+ intervention, we will also analyze the intervention effect according to whether participants received a “minimum dose” of the intervention. In order to assess whether the presence of comorbid mental health and substance use diagnoses, race, and language may modify the treatment effect, we will evaluate interaction terms between these pre-determined potential moderators and the treatment variable in the overall sample, and further conduct stratified analyses among these potential modifiers to assess the robustness of any differential effects if detected above.

We will report our results according to CONSORT guidelines.

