## **4. Analysis principles**

### **4.1 General principles for analysis of outcomes**

The primary analyses are based on intent-to-treat. Because participants may receive varying “doses” of the intervention, we also analyze the intervention effect according to whether participants received a minimum dose of the intervention.

In order to assess whether the presence of comorbid mental health and substance use diagnoses, race, and language may modify the treatment effect, we will evaluate interaction terms between these pre-determined potential moderators and the treatment variable in the overall sample, and further conduct stratified analyses among these potential modifiers to assess the robustness of any differential effects due to effect modification.

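### SAP 5.5 adds stratified analyses by age, gender, race and language that do not depend on a detected interaction, and for age and gender no interaction is ever tested

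*Combined protocol and SAP*

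**What the plan says.** Protocol 12.3 sets out to learn "whether the presence of comorbid mental health and substance use diagnoses, race, and language may modify the treatment effect", and the SAP repeats this aim in 4.1 and 5.5. For those moderators, protocol 12.3 says "we will evaluate interaction terms between these pre-determined potential moderators and the treatment variable in the overall sample", and that the team will "further conduct stratified analyses among these potential modifiers to assess the robustness of any differential effects if detected above". SAP 5.5 repeats that sentence, including its closing condition. SAP 4.1 has the same moderators and interaction tests, with a slightly different ending.

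SAP 5.5 then adds a final sentence: "We conduct stratified analyses where we have adequate sample size (age, gender, race, language"). It is not tied to a detected interaction. It names age and gender, which are on neither moderator list, and leaves out the mental health and substance use diagnoses, which are on both. Elsewhere (protocol 12.3, SAP 5.3.2) age and gender appear only as example covariates that predict utilization.

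Adequate sample size, the age cut-points and the race categories are not defined. Neither document labels the subgroup analyses exploratory or adjusts for their number. The only significance rule is in protocol 12.3 and SAP 5.3.2: "We will note differences that are statistically significant at the" 0.05 level.

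**The concern.** A significant effect in one stratum and a non-significant effect in the other does not show that the two effects differ. Only a comparison of the strata, the treatment-by-factor interaction, addresses that. For race and language the plan has such a test, but the last sentence of SAP 5.5 does not make the strata wait for it. For age and gender the plan has no such test.

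What is at stake is how the secondary reporting is read. If the primary comparison is null, one nominally significant stratum could be presented as a group in which the intervention works, and nothing in the plan would check that reading.

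**Working it through.** **1. The plan's own figure.** The documents give no error rate for subgroups. They do give "a total sample size of 364 patients (N=182 in each arm"), with "statistical power of 0.90 and two-sided type I error rate of 0.05, accounting for 80% retention over a 12-month study period". This can be reproduced:
- Baseline mean: 4.3 + 10.2 = 14.5 visits. A 10% reduction is 1.45 visits.
- SD is not given. Assuming Poisson variance, SD = √14.5 = 3.81.
- n per arm = 2 × (1.960 + 1.282)² × 14.5 / 1.45² = 145. Then 145 / 0.80 = 181.25, rounded up to 182, or 364 in all.

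So 364 fits a single overall comparison at 0.05 under that assumption. No allowance for subgroup tests is visible.

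**2. The two sentences of SAP 5.5 side by side.**

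| | Moderator sentence | Final sentence |
|---|---|---|
| Factors | mental health and substance use diagnoses, race, language | age, gender, race, language |
| Interaction test | yes | none for age or gender |
| Strata depend on a detected effect | yes | no |
| Selection rule | named in advance | sample size, undefined |

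The final sentence cannot be only a restriction of the one before it, because a restriction could not bring in age and gender.

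**3. Chance of a significant stratum with no true effect.** Inputs from the documents: 364 patients, 182 per arm, two-sided 0.05, and about 82.5% English-speaking (midpoint of the 78% and 87% in SAP 4.2). Assumed: every stratum tested at 0.05, factors independent of each other, 50/50 splits for age, gender and two-level race, and unequal splits for race with more levels.

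The two strata of one factor share no patients, so one two-level factor gives 1 − 0.95² = 9.75%. Strata of different factors do share patients, so multiplying across factors overstates the rate: 1 − 0.95⁸ = 33.7% is too high for eight strata. The overlap was handled by simulation (20,000 null trials, normal outcome):

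| Result with no true effect | Chance |
|---|---|
| Age and gender only (4 strata) | about 16% |
| Four two-level factors (8 strata) | about 25% |
| Race with three levels (9 strata) | about 29% |
| Race with four levels (10 strata) | about 32% |
| All four factors, benefit direction, primary not significant | about 11% (two-level race) to 14% (four-level race) |
| Age or gender, benefit direction, primary not significant | about 6% |

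Other runs with the same numbers of levels gave 25% to 27%, about 30%, and 33% to 34% for the second to fourth rows. Skewed negative binomial counts in place of normal outcomes gave essentially the same rates.

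**4. Effect of an interaction condition.** With four two-level factors, counting a stratum result only when that factor's interaction is also significant at 0.05 lowers the rate from about 25% to about 12%.

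**The case against.** The strongest reply is that SAP 5.5 speaks of stratified analyses and not of stratum p-values or claims. The 0.05 sentence in SAP 5.3.2 follows the between-arm comparison on the composite outcome, so applying it to every stratum is inference. That stands, and the rates above are conditional on it. It also stands that most splits and the numbers of levels are assumed, and that correlation between factors, such as race and language, would lower the rates.

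Four stronger readings are tempting, and the documents do not support them.
- *A reader might infer that the added strata give a false finding in about a third of null trials.* With two-level factors it is about a quarter. A third needs about ten strata, or requires also counting the interaction tests that protocol 12.3 pre-specifies. Any significant interaction or stratum comes to about 35% to 39% with two- or three-level race, and the four interaction tests alone give about 18%.
- *A reader might infer that a false claim of benefit in women or in younger patients is likely after a null primary result.* It is about 6% for age and gender.
- *A reader might infer a breach of a stated 5% rate.* The 0.05 in protocol 12.2 and SAP 3.3 belongs to the primary outcome. No familywise rate for subgroups is stated.
- *A reader might infer that choosing factors by sample size inflates error.* By itself it does not, and the four factors are named. What remains is that the SAP already reports observed data (136 of 364 with zero visits, and baseline comparisons), so it does not show that the choice came before the data were seen.

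SAP section 2, which lists no major protocol amendments, adds little: an extra stratification need not count as major.

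**Conclusion.** The point holds as a minor one. SAP 5.5 adds strata that do not wait for an interaction, and two of the four factors lie outside the pre-determined list and have no interaction test. The plan therefore contains no test of differential effects by age or gender, yet produces results that invite that reading.

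If every stratum is tested at 0.05 and there is no true effect, at least one is significant in about 25% of trials with four two-level factors, about 29% to 32% with three- or four-level race, and about 16% for age and gender alone. The most misleading case, apparent benefit in some stratum beside a non-significant primary result, arises in about 11% to 14% across all four factors. The assumptions are independent factors and, apart from language, assumed splits. The primary analysis is not affected.

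**What to change.** Replace the last sentence of SAP 5.5 with:

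> Subgroup analyses are exploratory. For each pre-determined moderator, and for age and gender (labelled as added to the protocol list), the treatment-by-factor interaction is reported with its 95% CI. Stratum estimates are shown with CIs only, and no subgroup claim is made from a stratum result without a detected interaction.

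This extends the condition in protocol 12.3 to every factor and needs no new data. The cost is wording and two more interaction terms, and stratum p-values can no longer be presented as findings. The extra terms raise the chance of at least one false-positive interaction at 0.05. Treating the tests as independent, it goes from 1 − 0.95⁴ = 18.5% to 1 − 0.95⁶ = 26.5%, counting mental health and substance use as two moderators. The exploratory label covers that increase.
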